#### Secondary hypotheses: HBPTM + NCM will be more costly but also more cost-effective in reducing (a) SBP at 12 months and (b) stroke recurrence at 24 months than HBPTM alone

The principal measures of cost to be used in the study pertain to (i) intervention-related resource costs and (ii) overall direct health care costs. To assess cost differences in intervention and overall costs across interventions, we will first compare average patient costs across the two groups. Patient-level analyses of costs, similar to those described above for outcomes, will be used to produce regression-adjusted measures of cost-effectiveness for each intervention. Using methods consistent with the standards published in 1996 [68-70], we will conduct incremental cost-effectiveness analyses (CEAs) to assess the relative effects of the interventions on three time periods: intervention period (12 months), follow-up period (24-months post-randomization), and lifetime perspective. Measures of effectiveness in the intervention and follow-up period CEAs will be based on differences across intervention groups in (1) mean changes in SBP (mm Hg); (2) stroke recurrence; and (3) quality of life (as measured by EuroQoL scores). Bootstrapping procedures will be applied to obtain confidence intervals around all of our cost-effectiveness estimates. Sensitivity analyses will be used to examine key uncertainties about CEA findings by identifying variables that have the most dramatic effects on estimated CE ratios and examining the effects of changes in these measures/assumptions on CEA results.

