### Sample size and power analysis

The primary hypotheses are (a) a greater reduction in systolic BP over three waves of data: baseline, 6 and 12 months and (b) a lower 24-month stroke recurrence rate among the combined HBPTM + NCM group compared to the HBPTM alone group. Although there may be more than one episode of stroke per patient, given the sample size, we will combine all events. We assume separate analyses of the outcomes, with pre-specified α = 0.05 for each outcome. Statistical modeling procedures will be used that allow the inclusion in the analysis of participants who do not complete the follow-up assessment (on an intent-to-treat basis). The approach to the power calculations incorporates the design feature of clustering. The cluster size of participants who are eligible (uncontrolled hypertension with a history of stroke) within PCP is estimated to range from 5 to 6. Data from a similar study of telemedicine (IDEATel) delivered to New York City Hispanics and Blacks did not show heterogeneous variances [60], so this scenario was not included in power calculations. Specific types of selection bias and attrition were considered.

Based on studies of telemedicine in Blacks and Hispanics [42,43,60-62], it was estimated that the baseline and longitudinal standard deviations of SBP at baseline will be between 18 and 22 mm Hg. The observed mean differences were from 3 to 8 for SBP. We posited that the enhanced telemedicine intervention will result in an effect size ranging from a 6- to 8-point difference in SBP. The assumptions were as follows: α = .05 for a two-tailed test; 1-β = .80 and above; and δ = μ_1_-μ_2_ = 6, 7, 8 (SBP point reduction). The following assumptions were used in the power calculations: R = 0.90 (reliability); g = 2 (groups), pooled σ = 20.75 (baseline control: 19.6; intervention 19.2; 6 month control: 21.7; intervention: 20.5; 12 month control: 21.0; intervention: 22.3), d = δ/σ (where δ is difference in end study and d is Cohen’s d;) [63]. The cluster size was estimated as 5; the intracluster correlation (ICC) = 0.03; and Vif = 1+ (clustersize-1)*ICC = 1.12.

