#### Summary

Conservatively, under the assumptions specified above, 225 subjects per group will provide power ≥0.80 to detect the hypothesized 6 to 8 unit differential change in SBP, based on testing the Time X Group interaction in a mixed model, adjusting for unreliability, design effects due to clustering and serial correlations. This sample size will also provide power ≥ 0.80 to detect the hypothesized 10% group reduction in the rate of stroke at 24 months from a baseline rate of 15%.

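### A bootstrap interval on a cost-effectiveness ratio loses its meaning if the effect difference is near zero, and without a value threshold it cannot settle the secondary hypothesis

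*Protocol article*

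**What the plan says.** The secondary-hypothesis part of the Analytic plan predicts that "HBPTM + NCM will be more costly but also more cost-effective in reducing (a) SBP at 12 months", and likewise for stroke recurrence at 24 months. It states that "we will conduct incremental cost-effectiveness analyses (CEAs) to assess the relative effects of the interventions on three time periods": 12 months, 24 months and lifetime. For the first two periods the effect measures are between-group differences in "1) mean changes in SBP (mm Hg); (2) stroke recurrence; and (3) quality of life (as measured by EuroQoL scores". Uncertainty is handled as follows: "Bootstrapping procedures will be applied to obtain confidence intervals around all of our cost-effectiveness estimates". The sensitivity analyses work by "identifying variables that have the most dramatic effects on estimated CE ratios", which shows that the ratio is the intended summary. Patient-level cost analyses "will be used to produce regression-adjusted measures of cost-effectiveness for each intervention". The article gives no willingness-to-pay value and no rule for calling one arm more cost-effective. It neither mentions nor excludes net benefit, the cost-effectiveness plane or acceptability curves, and it does not say which kind of bootstrap interval is meant.

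**The concern.** The incremental ratio is ΔC/ΔE, the cost difference over the effect difference, and it is well behaved only while ΔE stays away from zero. If the joint distribution of (ΔC, ΔE) crosses ΔE = 0, two things go wrong. First, the ratio is discontinuous: with ΔC positive, it runs to plus infinity as ΔE falls to zero and comes back from minus infinity once ΔE is negative. Secondly, its sign is ambiguous: ΔC > 0 with ΔE < 0 (dominated) and ΔC < 0 with ΔE > 0 (dominant) both give a negative value. Replicates can then no longer be ranked from good to bad, and lower and upper limits taken from them do not bound a set of plausible values.

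The second difficulty exists even when ΔE is clear of zero. If the combined arm is both dearer and more effective, the ratio is a price per mm Hg or per stroke averted. Whether that price is good value depends on what the payer would give for the unit of effect, and no such value is stated. The Discussion presents the cost-effectiveness result as a possible basis for wider coverage, so its uncertainty statement has to be readable.

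**Working it through.** The article gives no cost difference, cost variance or willingness-to-pay value, so no ratio or net benefit can be computed. What can be checked is how often the effect difference, which is the denominator, is indistinguishable from zero.

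**Inputs from the article**
- Sample size and power analysis: pooled SD 20.75; reliability 0.90; design effect 1 + (5 − 1) × 0.03 = 1.12; "α = .05 for a two-tailed test"; posited SBP difference 6-8 mm Hg; differences observed in earlier studies 3 to 8 mm Hg.
- Power for comparing rates of change in SBP: 225 per group; pre-post correlation ρ = 0.5 or 0.6.
- Power for stroke recurrence: 15% at 24 months with a 10% reduction, read here as absolute (15% to 5%).
- Background: 31% lower recurrence risk per 10 mm Hg.

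**The plan's own figure first.** The Summary states that "225 subjects per group will provide power ≥0.80 to detect the hypothesized 6 to 8 unit differential change in SBP". With ρ = 0.5 the SD of the change is 20.75 × √(2 × 0.5) = 20.75. With 225/1.12 × 0.90 = 180.8 per arm, power at 6 mm Hg is 0.785. It is 0.826 without the reliability penalty and 0.867 with ρ = 0.6. At 8 mm Hg it is 0.956. For 15% versus 5%, power is 0.89 to 0.92. The statement is reproduced to within 2 percentage points. The separate range of 208 to 223 per group for stroke was approached (199 to 207) but not matched exactly.

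**Formulas.** With z = d/SE:
- P(95% interval includes 0) = 1 − Φ(z − 1.96) − Φ(−z − 1.96).
- P(estimate has the wrong sign) = Φ(−z). This is also the share of bootstrap replicates at or below zero when the estimate equals d.
- SBP: SE = SD × √(2/n). Stroke: SE = √[(p₁q₁ + p₂q₂)/n].
- n = 225/1.12 = 200.9 per arm unless stated.

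**SBP.** SE = 20.75 × √(2/200.9) = 2.07. With the reliability penalty, SD = 20.75/√0.90 = 21.87 and SE = 2.18.

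| True difference | z | Interval includes 0 | Replicates ≤ 0 |
|---|---|---|---|
| 8 mm Hg | 3.86 to 3.67 | 3-4% | about 0.01% |
| 6 mm Hg | 2.90 to 2.75 | 17-22% | 0.2-0.3% |
| 3 mm Hg | 1.45 to 1.37 | 70-72% | 7-8% |

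Under the most favourable reading (ρ = 0.6, no design effect), SE = 20.75 × √0.8 × √(2/225) = 1.75. The interval then includes zero in 60% of trials at 3 mm Hg, 7% at 6 and under 1% at 8.

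**Stroke at the design effect.** 15% versus 5%: SE = √[(0.1275 + 0.0475)/200.9] = 0.0295 and z = 3.39. The interval includes zero in 8%.

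**Stroke at the effect implied by the Background.** The relative risk is 0.69^0.6 = 0.80 for 6 mm Hg and 0.69^0.8 = 0.743 for 8 mm Hg.
- 6 mm Hg: 15% versus 12.0%, difference 0.030, SE 0.034, z = 0.88. The interval includes zero in 86%; wrong sign in 19%.
- 8 mm Hg: 15% versus 11.1%, difference 0.039, SE 0.034, z = 1.15. The interval includes zero in 79%; wrong sign in 13%.

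As an intermediate case, 15% versus 10% gives z = 1.52 and 67%.

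**EuroQoL.** The article gives no SD or expected difference. If the SD is assumed to be 0.20-0.30 and the difference 0.02-0.05, the interval includes zero in 29-90%.

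**The case against.** The strongest reply is that the planned procedure is not itself wrong. A joint bootstrap of costs and effects is the usual basis for the cost-effectiveness plane, acceptability curves and net benefit. The article excludes none of these and specifies no percentile interval. A journal article may also leave the form of the uncertainty analysis and the value thresholds to a fuller plan. This stands to the extent that the absence of such detail is not an error. What the article does fix is the hypothesis, the ratio as the summary and an interval around it, and that combination is open to comment.

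The second reply is that the large percentages come from effects smaller than those planned. That is correct. However, 15% to 5% is a two-thirds reduction, whereas the article's own citation gives about 20-26% for a 6-8 mm Hg difference, and 3 mm Hg is the bottom of its own observed range. A summary of uncertainty should survive such results.

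A reader might also take the wording about measures for each intervention to mean a within-arm SBP change per dollar, inflated by regression to the mean in patients selected for SBP of at least 140 mm Hg. The text does not support this. It goes on to plan incremental analyses with effectiveness taken from differences between groups. Both arms passed the same screen and were randomised 1:1, so regression to the mean cancels in expectation.

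**Conclusion.** The point holds in a conditional form. An interval on cost per stroke averted is likely to be unreadable if the stroke effect is what the Background implies (the effect interval includes zero in about 79-86% of trials; wrong sign in 13-19%). The same applies to cost per mm Hg if the SBP effect is near 3 mm Hg (about 60-72%). At the stated design effects the problem is uncommon: about 3-22% for SBP at 6-8 mm Hg and 8% for stroke.

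Separately, and whatever the effect size, a ratio interval without a threshold cannot decide whether the dearer arm is more cost-effective.

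Two stronger conclusions are tempting and are not supported. One is that all the intervals will be uninterpretable; the figures at the design effects contradict it. The other is that net benefit is the only remedy; Fieller intervals, the joint bootstrap distribution and acceptability curves also deal with the instability.

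The figures rest on a normal approximation, no further loss to follow-up (no rate is stated), an absolute reading of the 10% stroke reduction for the design case, and the cited 31% per 10 mm Hg applying to this population.

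**What to change.** In the cost-effectiveness part of the Analytic plan:

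1. State that patient-level costs and effects are resampled jointly, within arm.
2. For each effect measure (SBP, stroke recurrence, EuroQoL), make the uncertainty summary the cost-effectiveness plane together with an acceptability curve or incremental net benefit, over a willingness-to-pay range fixed in advance.
3. Report the ICER as a point estimate. Add a ratio interval, for example Fieller, only where the effect difference is clearly away from zero.
4. Say that the conclusion on cost-effectiveness rests on the incremental comparison, and not on measures computed separately for each intervention.

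The data and the bootstrap are unchanged, so this is a change of wording in the plan. The real cost is having to choose and defend a value range per mm Hg and per stroke averted, for which the article gives no figures.

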#### Exploratory analysis of potential mediators and moderators

We will conduct exploratory analyses to test potential mediating pathways involving (1) changes in other stroke risk factors (that is, lipids, blood glucose); (2) changes in health behaviors (that is, diet, physical activity, medication adherence); and (3) antihypertensive medication intensification (that is, adding or changing dose or class of medications). We will first compare effects of the two interventions on each of these outcomes, following the analysis plans detailed above for continuous and dichotomous variables as appropriate. We will then use formal tests to examine the extent to which the intervention effects are mediated through these variables. Since we have no reason to assume that effects of the interventions will differ by race/ethnicity or by site, our primary analyses do not stratify by these factors or include interaction effects. That said, we will conduct exploratory analyses to examine whether or not the interventions are equally effective for Black and Hispanic patients, and across study sites [71-73].

## Discussion

Disparities in stroke remain a major public health problem in the United States. There is an urgent need for secondary prevention strategies that can help to reduce disproportionately higher rates of recurrent stroke among Black and Hispanic patients. Many interventions to improve BP control have been developed and tested, and several have been proven effective under controlled conditions [74-77]. However, if these interventions cannot find a place in primary care practices, their impact on public health will be negligible. Progress toward this goal has been hindered by lack of comparative effectiveness and cost-effectiveness data, particularly in minority populations, and insufficient utilization of health information technology that is needed to support their dissemination and long-term sustainability in community-based primary care practices where the majority of low-income minority patients receive their care. Two potentially viable interventions in this respect are home BP monitoring and telephone-based NCM, both of which have proven efficacy in improving BP control and may reduce the risk of recurrent stroke. Adoption of these interventions at the primary care level may also reduce the risk of incident stroke, which contributes even more heavily than recurrent stroke to disparities [78].

A major limitation of previous studies of NCM and home BP monitoring is their lack of sustainability and scalability. This is largely due to the intensive nature of the delivery of these interventions, which often requires multiple office visits and patient counseling sessions. The ongoing stroke telemonitoring hypertension trial addresses this limitation by using well-established web-based and wireless technologies, which are easily deployable, efficient and potentially cost-effective. The merging of two established and effective interventions along with the utilization of health information technology supports the sustainability of the HBPTM + NCM intervention and feasibility of its widespread implementation. Embedding care mangers within practices further facilitates sustainability particularly in the current climate of outcome-based payment reform. Cost-effectiveness analysis is an integral objective of this study given the enormous financial burden of stroke. The American Heart Association projects that direct costs of stroke will increase 238% from 2010 to 2030 and indirect costs will increase 73%; total costs are projected to increase from $53.9 billion in 2010 to $140 billion in 2030 [79]. Thus cost-effective secondary stroke prevention interventions have the potential to produce enormous savings, particularly in the care of minority patients who suffer disproportionately higher stroke-related morbidity and mortality.

If successful, these telehealth interventions can be relatively easily adapted and incorporated into the care of 1.4 million New Yorkers who receive care within the HHC network. MetroPlus, HHC’s 420,000-member health plan, already reimburses for the House Calls program among patients with poorly controlled diabetes and congestive heart failure. Demonstrating the comparative- and cost-effectiveness of this program among stroke patients with uncontrolled hypertension may facilitate the process of expanding coverage for this intervention for this high-risk population as well. Ultimately, we envision implementation beyond our study population across the larger HHC community and other local healthcare systems, as well as other urban communities that, like NYC, have large populations of underserved minorities who would benefit from secondary stroke prevention interventions.

## Trial status

Recruitment for this study began in December 2013 and is ongoing.

## Abbreviations

BP: blood pressure
CEA: cost-effectiveness analysis
EHR: electronic health record
HBPTM: home blood pressure telemonitoring
HHC: Health and Hospital Corporations
IRB: institutional review board
NCM: nurse case management
RA: research assistant
RCT: randomized controlled trial
SBP: systolic blood pressure
